### Analysis

Qualitative analysis of interview and focus group data (phases 1 and 2) will be performed using an iterative analysis process where investigators will review interview transcripts and search for key phrases, ideas, and themes directly pertaining to the research questions. Similarly, the qualitative comments and feedback obtained from questionnaires in phases 3 and 4 will also be transcribed and analyzed for themes. The information collected in phases 1 and 2 will be used to develop the e-CBT modules, with the information collected through phases 3 and 4 being used to finalize the format of the e-CBT (if necessary).

In phases 3 and 4, the relationship between socioeconomic status, demographic factors, and mental health challenges faced by CWs will be investigated. Questionnaire data will initially be examined for missing, nonsensical, and outlying variables and corrected where possible. Missing data will be treated as missing and not imputed (ie, will be analyzed on a per-protocol basis).

Following this, the symptomatology questionnaires (DASS-42, Q-LES-Q, QIDS-SR16, PHQ-9, GAD-7, and PCL-5) will be analyzed based on score change from baseline to posttreatment, 6-month follow-up, and 12-month follow-up. Questionnaire scores will be calculated for each time point, and then the changes between the times will be assessed using multivariate repeated measures analysis of variance (MANOVA). Comparisons will then be made between the e-CBT and control arms using linear regression models while controlling for demographic variables (eg, age, gender).

Factoring in anticipated dropouts, recruitment numbers have been purposely oversampled. From previous research in similar patient populations, dropouts can be expected to be up to 25% [61]. Given that there are 6 specialized versions of the e-CBT modules with different symptom questionnaires, it is difficult to calculate a single sample size or provide specific power calculations. However, using the PCL-5 as an example as it will be common to all participants, a 10-point change is considered clinically significant [62]. Therefore, a sample size of 30 participants in each arm will be sufficient for detecting significant results with *P*=.05 and a power of 0.8.

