CWs (n=100; 50 men, 50 women) meeting the inclusion/exclusion criteria will complete a set of socioeconomic, demographic, and the following clinical questionnaires (primary diagnosis dependent) at baseline: Depression and Anxiety Stress Scale - 42 Item (DASS-42), Quality of Life Satisfaction and Enjoyment Questionnaire (Q-LES-Q), Quick Inventory of Depressive Symptoms Self Report - 16 Item (QIDS-SR16), Patient Health Questionnaire - 9 Item (PHQ-9), Generalized Anxiety Disorder - 7 Item (GAD-7), and PTSD Checklist for the DSM-5 (PCL-5) [55-60]. Questionnaires and e-CBT modules will be completed through the Online Psychotherapy Tool (OPTT; OPTT Inc.), a secure, cloud-based, mental health care delivery, online platform. OPTT can be accessed from various devices (ie, computer, cellphone, tablet) and internet browsers. Following the initial assessment, participants will be randomly allocated to the e-CBT + TAU (n=50; 25 men, 25 women) or TAU (n=50; 25 men, 25 women) arm.

Participants in the e-CBT group will be assigned to 1 of the 6 therapy modules based on their gender and diagnosis (ie, female/male; GAD/MDD/PTSD). All e-CBT sessions will be completed through OPTT. Sessions will be designed to mirror in-person CBT content and consist of approximately 30 slides and interactive therapist videos (40-60–minute completion time), with 12 sessions in total (1 module per week). The modules will focus on standard aspects of CBT (the connection between thoughts, behaviors, emotions, physical reactions, and environment) and incorporate different skills into each session (eg, mindfulness, goal setting, activity scheduling). Each participant will be assigned a specific therapist who will be their care liaison through the program. Each week, the clinician will send the new e-CBT session to the participant through OPTT on a predetermined day of the week. Each of these sessions will include a homework assignment that the participant must send back to their clinician by a predetermined date to gain access to the next session. Upon receiving the homework submission, the clinician will review the participant’s work and provide individualized feedback on their performance. This feedback will be sent back to the participant with their new e-CBT module the following week. Clinician feedback will follow a structured format and take approximately 15 minutes per patient, allowing for increased scalability.

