Participants in both arms will complete the symptomology questionnaires every 2 weeks along with 6-month and 12-month follow-ups. Additionally, participants in the e-CBT arm will complete a qualitative questionnaire regarding their experience using OPTT. These questions will relate to the aesthetic appeal of OPTT, the intuitiveness of OPTT, technical support experience, OPTT navigation and simplicity, and the kinds of devices used to access therapy. Information from this qualitative questionnaire will be used to fine-tune the e-CBT modules for phase 4.

### Phase 4

At baseline, participants (n=100; 50 men, 50 women) will complete the same socioeconomic, demographic, and clinical questionnaires as in phase 3 through OPTT. Following the initial assessment, participants will be randomly allocated to either the e-CBT + TAU (n=50; 25 men, 25 women) or in-person CBT + TAU (n=50; 25 men, 25 women) arm. Participants in the TAU arm will continue with current lifestyle choices (ie, physical activity, diet, socialization) and current treatments (ie, pharmacotherapy, meditation) for the duration of the program.

Participants in the e-CBT arm will receive a specific program based on their primary diagnosis and gender (male/female; GAD/MDD/PTSD). Participants will be assigned a specific therapist who will be their care liaison throughout the program. Participants in the in-person CBT arm will receive similar content, homework, and feedback compared to the e-CBT arm. All in-person CBT sessions (60-75–minute completion times) will be delivered by a trained professional.

Participants in both arms will complete the symptomology questionnaires biweekly (same as in phase 3) along with 6-month and 12-month follow-ups. Following week 12 (posttreatment), participants will also complete an additional MINI. Additionally, participants in the e-CBT arm will complete the same qualitative questionnaire relating to their experience using OPTT. These responses will be discussed with the end-user expert group to form recommendations for improving the e-CBT modules through OPTT.

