### Outcomes

Phases 1 and 2 will be completed using qualitative individual interviews along with focus groups. Phases 3 and 4 will be completed using the quantitative methodology and will be based on the findings from phases 1 and 2.

Phase 1 aims to evaluate mental health challenges and barriers to receiving care faced by CWs. This information will be used to create the e-CBT modules that will be presented to participants in phase 2, where the usability of these modules will be investigated.

In phases 3 and 4, the primary outcome will be comparing changes in symptom severity from baseline to posttreatment between e-CBT and TAU/in-person CBT arms, respectively. This will be evaluated using the DASS-42, Q-LES-Q, QIDS-SR16, PHQ-9, GAD-7, and PCL-5. These questionnaires will be completed biweekly starting at baseline until posttreatment (week 12), followed by 6-month and 12-month follow-ups.

The secondary outcomes of phases 3 and 4 will be evaluating how personal, social, and demographic factors can impact treatment experience. This will be investigated using the data from the qualitative questionnaires.

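### An undefined per-protocol analysis is the only one stated for the Phase 3 and 4 comparisons; with up to 25% dropout it no longer rests on randomisation and may be biased

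*Protocol article*

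**What the plan says.** The Analysis section of the protocol article sets the rule for Phases 3 and 4: "Missing data will be treated as missing and not imputed (ie, will be analyzed on a per-protocol basis". No other analysis population is named there, and no mixed model or sensitivity analysis. The per-protocol set is not defined.

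The stated methods are a repeated-measures MANOVA of the changes over time, followed by linear regression comparing the arms with adjustment for demographic variables. The Outcomes section makes the between-arm comparison of change from baseline to posttreatment the primary outcome of both phases. It also says of the symptom scales: "These questionnaires will be completed biweekly starting at baseline until posttreatment (week 12").

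On attrition, the Analysis section says that "dropouts can be expected to be up to 25" per cent. Its only answer is this: "Factoring in anticipated dropouts, recruitment numbers have been purposely oversampled". It adds that, for a 10-point PCL-5 change, "a sample size of 30 participants in each arm will be sufficient".

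The Phase 3 section puts a condition on the e-CBT arm alone: "Each of these sessions will include a homework assignment that the participant must send back to their clinician by a predetermined date". Meeting it opens the next session. In Phase 4 the comparator is the "in-person CBT + TAU (n=50; 25 men, 25 women) arm", which is described as having content, homework and feedback similar to e-CBT.

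**The concern.** Not imputing is a decision about missing values. Per-protocol is a decision about who is analysed. Neither implies the other, and a likelihood-based mixed model imputes nothing yet keeps everyone. By joining the two, the article leaves it unclear who will be analysed and commits the efficacy question to a subset formed after randomisation.

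The stated methods point the same way. A participant without a week-12 score has no posttreatment change and cannot enter the regression. A classical repeated-measures MANOVA ordinarily drops any incomplete record. Scores collected every two weeks before a participant left would go unused in the between-arm comparison.

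At stake is the primary comparison in both randomised phases. If leaving is related to how a participant is doing, and that relation or the dropout rate differs between arms, the completer difference no longer estimates the effect in those randomised.

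**Working it through.** **1. The article's own sample-size figure.** Inputs from the Analysis section: difference 10, alpha 0.05, power 0.80, 30 per arm. No SD is given, so 30 cannot be reproduced, only back-solved. From n = 2(z₁ + z₂)²SD²/10², SD = 10·√(30/2)/(1.96 + 0.84) ≈ 13.8 (two-sided; 13.6 with the t distribution). One-sided it is 15.6. I use 13.8 below as an assumption.

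**2. Does oversampling cover the loss of numbers?** Needed: 30/(1 − 0.25) = 40 per arm. Planned: 50. Expected to remain: 50 × 0.75 = 37.5, above 30. So yes, by the article's own figures. Power for 10 points depends on the SD:

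| SD (assumed) | 30 per arm | 37 per arm | 50 per arm |
|---|---|---|---|
| 12 | 0.90 | 0.95 | 0.99 |
| 13.8 | 0.80 | 0.88 | 0.95 |
| 16 | 0.68 | 0.77 | 0.88 |

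This concerns numbers only and says nothing about who remains.

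**3. Bias of a completer comparison.** In one arm, let d be the proportion dropping out and g the mean improvement of completers minus that of dropouts. The completer mean exceeds the mean of all randomised by d·g. The between-arm bias towards e-CBT is therefore

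d(e-CBT)·g(e-CBT) − d(control)·g(control).

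The article gives neither d by arm nor g. With assumed values, in PCL-5 points:

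| Dropout, e-CBT / control | g, e-CBT / control | Bias towards e-CBT |
|---|---|---|
| 25% / 25% | 10 / 10 | 2.5 − 2.5 = 0 |
| 25% / 10% | 10 / 10 | 2.5 − 1.0 = +1.5 |
| 25% / 25% | 10 / 0 | 2.5 − 0 = +2.5 |
| 10% / 25% | 10 / 10 | 1.0 − 2.5 = −1.5 |
| 25% / 25% | 5 / 10 | 1.25 − 2.5 = −1.25 |

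If g is 0 in both arms, the bias is 0 whatever the dropout.

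**4. Effect on the test.** Simulation with no true effect: 50 per arm, SD of change 13.8, probability of dropout logistic in the participant's own change (one logit per SD where it is outcome-related), t-test on completers, 4,000 runs per scenario.

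| Dropout, e-CBT / control | Outcome-related in | Bias towards e-CBT | Type I error |
|---|---|---|---|
| 25% / 25% | neither arm | 0.0 | 5.2% |
| 25% / 25% | both, same mechanism | +0.1 | 4.6% |
| 25% / 10% | both | +1.7 | 9.4% |
| 25% / 25% | e-CBT only | +3.0 | 16.3% |
| 10% / 25% | both | −1.6 | 8.5% |
| 25% / 25% | control only | −2.9 | 14.6% |

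The bias is proportional to the SD. The largest entry would be 2.96 × 12/13.8 = 2.6 at SD 12 and 2.96 × 16/13.8 = 3.4 at SD 16; the type I error would not change. A scenario in which poor responders leave e-CBT while good responders leave control gave 5.9 points and 48%. I leave it out of the range because nothing in the article suggests it.

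**5. What the documents say about direction.** In Phase 3 only the e-CBT arm has a weekly homework condition, so poorly responding participants could plausibly be lost mainly from that arm. In Phase 4 both arms have homework, and the Introduction names irregular work hours as a barrier to care, so the in-person arm could lose more. The direction there is open.

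**The case against.** The strongest reply is that the article does not show a biased comparison. It gives one overall dropout figure, with no split by arm and no reasons. Equal dropout with an equal mechanism gives no bias, and higher dropout in the control arm can turn it against e-CBT. This stands: bias is a risk, not a fact. A reader might infer that both phases are tilted towards e-CBT, but the homework asymmetry on which that rests exists only in Phase 3.

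A reader might also infer that participants who miss homework will be excluded, leaving only the motivated in the e-CBT arm. The article does not say so. The homework condition governs access to the next session, not to the questionnaires, which both arms complete every two weeks. Since per-protocol is explained only as not imputing, an adherence exclusion is one possible reading of an undefined set.

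Nor is it right that missing data receive no handling. Questionnaire data are examined for missing, nonsensical and outlying values and corrected where possible, and a rule is stated. Leaving data unimputed would be acceptable within a mixed model.

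Finally, a bias of 1.5 to 3 points is 15% to 30% of the article's 10-point benchmark. That is modest, yet enough in the simulation to raise the false-positive rate to between about 9% and 16%.

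None of this defends a sole per-protocol analysis. An unknown direction of bias is a reason to avoid it. The sentence is also a positive rule in the article, not a detail left to a later analysis plan, which would be expected to inherit it.

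**Conclusion.** The point holds as a defect of the stated rule. The rule conflates non-imputation with a per-protocol population, leaves that population undefined, and makes it the only basis for the primary comparison in Phases 3 and 4, with up to 25% dropout expected. Losing participants without a posttreatment score takes away the protection of randomisation, and oversampling does not restore it.

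The consequence is possible bias: plausibly towards e-CBT in Phase 3, of unknown direction in Phase 4. Its size is illustrative: 0 if rate and mechanism match between arms, about 1.5 to 3 PCL-5 points either way if they do not, with type I error from about 5% to 16%. These figures rest on an SD of 13.8 back-solved from 30 per arm, on assumed dropout splits, and on assumed links between dropout and outcome. None of these is in the article. Confidence is high in the defect of wording and low in any particular size or sign.

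**What to change.** Replace the sentence in the Analysis section with a rule to this effect: the primary analysis in Phases 3 and 4 includes all randomised participants in the arm assigned, using a likelihood-based mixed model for repeated measures on all biweekly scores to week 12, with arm-by-time terms and baseline score as covariate, without imputation and valid under missing at random.

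In addition:

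- State that the scheduled questionnaires continue for participants who stop sessions.
- Add one missing-not-at-random sensitivity analysis, such as a delta-adjusted or reference-based one. It is needed because the dropout simulated above depends on the outcome itself, which a mixed model would not necessarily correct in full.
- Define the per-protocol set and keep it as supportive. For any claim in Phase 4 that e-CBT is comparable to in-person CBT, show it beside the all-randomised analysis.
- Report dropout by arm.

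The cost is wording, a standard model and a little more analysis. No new assessments are scheduled and no larger sample is needed: at the back-solved SD, 37 per arm already give power of 0.88. The downside is that the estimated effect may be smaller than the completer estimate.

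### The repeated-measures MANOVA drops every participant with an incomplete record and tests change over time rather than the treatment effect; one mixed model per scale would do better with the same data

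*Protocol article*

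**What the plan says.** All references are to the protocol article.

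- **Method (Methods, Analysis).** Scores are calculated for each time point, "and then the changes between the times will be assessed using multivariate repeated measures analysis of variance (MANOVA". The arms are then compared by linear regression adjusted for demographic variables.
- **Outcomes entered (Analysis).** The plan is that "the symptomatology questionnaires (DASS-42, Q-LES-Q, QIDS-SR16, PHQ-9, GAD-7, and PCL-5) will be analyzed based on score change from baseline to posttreatment", and also to the 6-month and 12-month follow-ups. That makes four named time points including baseline.
- **Collection schedule (Outcomes).** "These questionnaires will be completed biweekly starting at baseline until posttreatment (week 12), followed by 6-month and 12-month follow-ups". That is seven assessments from baseline to week 12 plus two follow-ups, nine in all.
- **Missing data (Analysis).** "Missing data will be treated as missing and not imputed (ie, will be analyzed on a per-protocol basis". Dropout of up to 25% is expected.
- **Who completes which scale.** Phase 3 introduces "the following clinical questionnaires (primary diagnosis dependent) at baseline". Analysis repeats the idea: "Given that there are 6 specialized versions of the e-CBT modules with different symptom questionnaires". It then justifies its sample-size example by "using the PCL-5 as an example as it will be common to all participants", and says this of no other scale. The later Phase 3 text ("Participants in both arms will complete the symptomology questionnaires every 2 weeks along with 6-month and 12-month follow-ups") and Outcomes make no such distinction and read as if everyone completes the whole set.
- **Primary outcome (Outcomes).** In phases 3 and 4 it is the comparison between arms of change in symptom severity from baseline to posttreatment.

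**The concern.** Three features fit together poorly.

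First, classical repeated-measures MANOVA works on complete records: one missing value among the modelled variables removes the participant. Without imputation and with up to a quarter dropping out, the analysed group is smaller than the randomised one and selected on having stayed.

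Second, whether the model can be fitted at all depends on which scales each participant completes, and the article does not settle that.

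Third, the repeated scores are put to the wrong question. Change over time can appear in both arms for reasons unrelated to treatment, such as regression to the mean. The question of interest is whether change differs between arms. That is left to a separate regression needing only two scores, so the weekly course of someone who leaves before week 12 adds nothing to it.

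At stake are precision, the representativeness of the analysed group, and the chance that an unplanned method replaces the stated one once the data are seen.

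**Working it through.** **Inputs.** From the article: 100 participants per randomised phase, 50 per arm; dropout d = 0.25 (an upper figure); six scales; four time points named for analysis; nine collected. The article does not say by when the 25% have left, so I take it as the total by the last time point. Assumption, not in the article: a further chance p of 2%, 5% or 10% of missing any one post-baseline visit, independently.

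**1. The plan's own figure.** The article states 30 per arm for a 10-point PCL-5 change at P=.05 and power 0.8. It gives no standard deviation, so the figure cannot be reproduced. Solved backwards (two-sided, normal approximation), it implies SD = 10 / [√(2/30) × (1.96 + 0.84)] = 13.8. Taken only as a yardstick, 30 / (1 − 0.25) = 40 per arm, so recruiting 50 covers the stated dropout.

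**2. Complete records, one scale at a time.** Complete out of 100 = 100 × (1 − d) × (1 − p)^(T − 1), for T time points.

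| p (assumed) | T = 4: of 100 | T = 4: per arm |
|---|---|---|
| 0 | 75 | 37.5 |
| 2% | 75 × 0.98³ = 71 | 35.3 |
| 5% | 75 × 0.95³ = 64 | 32.2 |
| 10% | 75 × 0.90³ = 55 | 27.3 |

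Only the last row falls below the plan's 30 per arm.

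**3. All six scales in one model.** Four time points give 6 × (4 − 1) = 18 within-person contrasts. The multivariate test needs error degrees of freedom (complete cases − 2 arms) of at least that number.

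- If everyone completes all six scales, 75 complete cases give 73 degrees of freedom, and the model can be fitted.
- If an assumed one third receive all six, 100 × 1/3 × 0.75 = 25 complete cases give 23 degrees of freedom, which barely exceeds 18.
- If no diagnosis receives all six, there are no complete cases and nothing can be fitted.

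The article's statements are compatible with any of these.

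**4. Which question each step answers.** The primary outcome is a difference between arms. The MANOVA is described as assessing change between times. The regression compares arms, and for the primary outcome it uses change from baseline to week 12. A participant who leaves after week 8 has five scores on a scale (weeks 0, 2, 4, 6, 8) and contributes none of them to that comparison.

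**5. Size of the alternative.** A mixed model with baseline as a covariate has 6 biweekly + 2 follow-up = 8 post-baseline visits. An unstructured covariance then has 8 × 9 / 2 = 36 parameters per scale.

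**The case against.** The strongest reply is that the primary comparison does not depend on the MANOVA. Outcomes defines a between-arm comparison, Analysis assigns it to linear regression, and the Abstract and Results name regression for the quantitative work. Regression on change to week 12 needs two scores on one scale and can be run whatever happens to the MANOVA. Leaving weeks 2 to 10 out of a week-12 comparison is common and costs efficiency; it is not in itself an error. All of this stands. What remains is that the regression, too, drops people without a week-12 score, and the plan has no step that uses their earlier ones.

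Several stronger readings are tempting, and the article does not support them:

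- **That most participants are discarded.** The plan's own dropout leaves 75 of 100. Even with 10% missed per visit, 55 remain over the four named time points.
- **That all nine assessments enter the model.** Over nine, the same assumptions would leave 64, 50 or 32, and a joint model would have 6 × 8 = 48 contrasts. The reference to each time point is loose, but the sentence before it names change at posttreatment, 6 months and 12 months.
- **That no participant has all six scales.** The article calls the scales diagnosis dependent without saying who receives what. Zero complete cases is the extreme of an ambiguity.
- **That the six scales are modelled jointly.** This is never stated. Scale by scale, four time points give 3 contrasts, which can be fitted even within one diagnosis: about 25 completers, assuming equal thirds.

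The choice between joint and per-scale modelling may be settled in a fuller plan that is not shown. The method, the missing-data rule and the conflicting statements about the scales are in this article.

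**Conclusion.** The concern holds in a limited form. As stated, the MANOVA loses about 25 of 100 participants from dropout alone, and about 29, 36 or 45 of 100 if a further 2%, 5% or 10% of visits are missed over four time points. The 25% is the plan's upper figure; the visit-level rates are assumptions. Failure to fit is conditional: it requires both a joint six-scale model and no diagnosis receiving all six scales, and the article establishes neither.

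The mismatch of question does not depend on those readings: the MANOVA is described as addressing change over time, while the treatment effect rests on a regression that makes no use of early leavers' scores. The primary comparison is weakened rather than broken. This should be changed, because a better method is available at little cost.

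**What to change.** Replace the MANOVA-then-regression sequence in phases 3 and 4 with one likelihood-based linear mixed model per scale:

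- **Terms:** arm, time, arm × time, baseline score, diagnosis and gender.
- **Population:** all randomised participants assigned that scale who have any post-baseline score, in place of the per-protocol wording.
- **Estimates:** the week-12 arm contrast as the treatment effect, with the 6-month and 12-month contrasts from the same model as secondary.
- **Covariance:** unstructured where it can be estimated, with a simpler structure prespecified as fallback. With 36 parameters, and perhaps about 33 participants on a scale given to one diagnosis only (100 / 3, assuming equal thirds), the fallback may be needed.

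Reconcile Phase 3, Outcomes and Analysis by stating which scales every participant completes and which depend on diagnosis.

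**Cost.** This is a change of wording. It uses data already scheduled for collection and standard software. The downside is small: the estimates rely on a missing-at-random assumption and on the covariance choice, and a participant with no post-baseline score still contributes nothing.

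### The between-arm regression on score change names only demographic covariates; without the baseline score of the same scale it loses precision and leaves the estimate exposed to chance baseline imbalance

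*Protocol article*

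**What the plan says.** Four statements in the protocol article bear on this.

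- **Primary outcome (Outcomes).** For Phases 3 and 4, "the primary outcome will be comparing changes in symptom severity from baseline to posttreatment between e-CBT and TAU/in-person CBT arms, respectively".
- **Response (Analysis).** The six questionnaires "will be analyzed based on score change from baseline to posttreatment, 6-month follow-up, and 12-month follow-up".
- **Models (Analysis).** First, "the changes between the times will be assessed using multivariate repeated measures analysis of variance (MANOVA". The arms are then compared "using linear regression models while controlling for demographic variables (eg, age, gender".
- **Data available (Phase 3, Phase 4).** The clinical questionnaires are completed at baseline, before allocation, in both phases. Primary diagnosis is established at entry and decides the e-CBT module: participants are "assigned to 1 of the 6 therapy modules based on their gender and diagnosis (ie, female/male; GAD/MDD/PTSD".

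The examples in the covariate list leave the choice of demographic variables open. They do not extend it to clinical ones. Neither baseline score nor diagnosis is mentioned as a covariate, and nothing says that either is excluded.

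**The concern.** The baseline score on a symptom scale is usually among the best predictors of the later score on that scale. Subtracting it is not the same as adjusting for it. Subtraction fixes the slope on baseline at 1, whereas the slope in the data is normally lower because extreme scores drift back towards the mean. This has two consequences. The residual variance is larger than it need be. And if one arm happens to start with worse scores, that arm tends to show more improvement whether or not the treatment works.

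The trial is small (50 per arm before dropout), so both the lost precision and the chance imbalance are large enough to matter, and the variable that removes them is already recorded.

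**Working it through.** **1. The plan's own figures.** The Analysis section gives 30 per arm for a 10-point PCL-5 difference, P=.05 and power 0.8, with dropout of up to 25%. It gives no SD, so 30 cannot be reproduced directly. Solving backwards (two-sided, normal approximation): SD = 10 × √(30/2) / (1.960 + 0.842) = 38.73 / 2.802 = 13.8. This is used below as the SD of the change score; it is an inference, not a figure in the article. Expected completers: 50 × 0.75 = 37.5 per arm.

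**2. Variance of the two analyses.** Let s0 and s1 be the SDs at baseline and posttreatment and r their correlation within arm.

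- Change score: s0² + s1² − 2·r·s0·s1
- Baseline-adjusted (ANCOVA): s1²(1 − r²)
- Difference: (s0 − r·s1)², which is never negative

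With s0 = s1 = s these become 2s²(1 − r) and s²(1 − r²), and their ratio is (1 + r)/2.

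**3. Numbers.** The documents do not give r. An assumed range of 0.3 to 0.7 gives:

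| r | Variance ratio | Extra participants needed by change score | SE ratio, change / ANCOVA | ANCOVA n per arm (v 30) | Power at 30 (v 0.80) | Power at 37 (v 0.875) |
|---|---|---|---|---|---|---|
| 0.3 | 0.65 | 1/0.65 − 1 = 54% | 1.24 | 20 | 0.94 | 0.97 |
| 0.5 | 0.75 | 1/0.75 − 1 = 33% | 1.15 | 23 | 0.90 | 0.95 |
| 0.7 | 0.85 | 1/0.85 − 1 = 18% | 1.08 | 26 | 0.86 | 0.92 |

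The n column is 30 × the ratio, rounded up. Power uses the back-solved SD of 13.8.

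**4. Shift from a chance imbalance.** The standard error of the baseline difference between arms is √(2/37.5) = 0.231 SD. The change-score difference moves by (1 − r) × imbalance, in favour of the arm that starts worse. A one-standard-error imbalance gives 0.7 × 0.231 = 0.16 SD at r = 0.3, 0.5 × 0.231 = 0.12 SD at r = 0.5, and 0.3 × 0.231 = 0.07 SD at r = 0.7. At r = 0.5 the change and the raw score have the same SD, so 0.1155 × 13.8 = 1.6 PCL-5 points.

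**5. Simulation check.** 20,000 trials per value of r, 37 per arm, no treatment effect.

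- Over all trials the change-score estimate averaged zero and type I error was 0.048 to 0.051. The model standard error matched the true spread (0.232 v 0.231 at r = 0.5).
- In trials where one given arm's baseline mean was more than 0.3 SD higher, the change-score effect shifted by 0.29, 0.20 and 0.13 SD, and type I error was 0.14, 0.12 and 0.08 (r = 0.3, 0.5, 0.7). ANCOVA stayed at zero, with type I error 0.045 to 0.053. Such an imbalance is not rare: 0.3/√(2/37) = 1.29 standard errors, about 10% of trials in each direction.
- The simulated variance ratios were (0.2214/0.2722)² = 0.66, (0.2024/0.2311)² = 0.77 and (0.1675/0.1804)² = 0.86. These include the small cost of estimating the slope and are close to the formula.

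**The case against.** **The article is condensed and the covariate list is open.** This stands for detail the article does not touch. It does not cover the baseline score: the article names the model and the class of covariates, and a same-scale baseline score is not in that class. It is also fair that the dependent variable is not named outright. Change score is an inference, although the Outcomes section and the sentences before the regression point the same way. The repeated-measures MANOVA does not fill the gap, because the comparison of arms is assigned to the regression.

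**The planned analysis is valid.** This stands. Randomisation makes the estimate unbiased on average, with correct type I error. The dependence on imbalance is conditional on the imbalance that occurs.

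**About 37 per arm already exceeds the 30 required.** True, but the margin rests on an SD the article does not state. At an SD of 15 the requirement is 36 per arm, and at 20 it is 63.

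**Stronger readings.** A reader might infer three further faults that the article does not support.

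- *Standard errors are understated.* Leaving out baseline or diagnosis makes them larger, not falsely small. Only unmodelled therapist clustering could understate them. The article says "Each participant will be assigned a specific therapist who will be their care liaison through the program", but gives no number of therapists, caseload or intraclass correlation. The Training section describes a standardised pathway, templates and psychiatrist approval of all feedback, which may limit therapist differences. Any inflation figure would simply return its assumptions, and a random effect estimated from few therapists is a debatable choice.
- *Randomisation ignores diagnosis.* The article gives target counts, "participants will be randomly allocated to the e-CBT + TAU (n=50; 25 men, 25 women) or TAU (n=50; 25 men, 25 women) arm", and does not list stratification factors. Those are commonly left to the full protocol.
- *Adjusting for diagnosis brings a large gain.* No figure supports this. Level differences between diagnoses cancel in a change score, and some questionnaires depend on the primary diagnosis.

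**Conclusion.** The point holds as a matter of efficiency and of robustness to chance imbalance, not of validity. As described, the between-arm regression does not name the one covariate that would help most. For assumed correlations of 0.3 to 0.7 and equal SDs at the two times, adding it is worth the same as recruiting 18% to 54% more participants. It also removes a shift of 0.07 to 0.16 SD for a one-standard-error baseline imbalance. The size depends on r, which the documents do not give. The direction does not, because apart from the minor cost of estimating one slope the adjusted variance is never the larger. The figures in PCL-5 points and the power values also rest on the SD of 13.8 inferred from the plan's own sample size. The article gives no ground for criticising the standard errors, the therapist structure or the randomisation list.

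**What to change.** In Phases 3 and 4, specify the between-arm model for each questionnaire as a linear regression with arm, the baseline score of the same scale, age and gender. The response can stay as change from baseline: once baseline is a covariate, the arm coefficient is the same for change as for the posttreatment score, so the primary outcome definition need not alter. The same model serves the 6-month and 12-month comparisons. Primary diagnosis, also already recorded, can be added for scales completed by more than one diagnostic group. That is a reasonable option rather than a necessity.

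The cost is a change of wording in the analysis section or SAP, best made before Phase 3 outcome data are seen, and one degree of freedom per model for the baseline score. No new data, visits or participants are needed.
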